## Abstract

**Background:**

The All4Children project addresses the urgent need to transition from institutionalization to family-based care for out-of-home children in Portugal. Despite evidence highlighting the detrimental effects of institutionalization, only a small percentage of children (less than 4%) are currently placed in family foster care in the country. In response to European directives for deinstitutionalization, Portuguese legislation now prioritizes non-kinship family foster care as the preferred alternative for young children in need of care. To facilitate this transition, the Integrated Model of Family Foster Care (MIAF) was developed, offering a comprehensive framework covering the entire spectrum of family foster care.

**Objective:**

This research aims to investigate the initial implementation stage of the MIAF to promote high-quality family foster care in Portugal.

**Method:**

The study will conduct a mixed-method and longitudinal research project in family foster care agencies across different regions of Portugal, focusing on evaluating the implementation and outcomes of the MIAF model using a multi-informant and multi-method approach. The participants will include caseworkers, children aged 0–9 years entering foster care, and their respective foster families enrolled in the MIAF program. Process evaluation will assess fidelity, feasibility, appropriateness, and acceptability of MIAF modules, while outcome evaluation will examine child safety, stability, well-being, as well as foster family well-being and quality of relational care.

**Outcomes:**

The insights gained from this research initiative will serve as a foundation for the ongoing enhancement of MIAF. Consequently, this project has the capacity to advance evidence-based child welfare practices by refining processes and strategies to better serve vulnerable children and youth.

**Conclusion:**

Facilitated by a multidisciplinary team, this project will contribute to advancing research in the field, enhancing practice, and informing policy during a pivotal stage of deinstitutionalization in Portugal.

## Introduction

Every child has the fundamental right to be raised in a responsive family environment that fosters their optimal development. Unfortunately, around 8 million children worldwide currently reside in institutional care [1]. Extensive research documenting the harmful effects of institutionalisation across various domains of child functioning, particularly on infants and young children, is well-established [2]. Equally well documented is the capacity for recovery following family foster care placement [3]. However, in Portugal in 2022, only 3.6% of all out-of-home children were placed in family foster care [4]. In alignment with the European calls-to-action for deinstitutionalization [5], the Portuguese law (e.g., Decree-Law 142/2015) has recently underscored non-kinship family foster care as the preferred alternative care measure for children up to the age of 6. As a result, the country recently implemented processes for recruiting, training, selecting foster families, and placement of children in these settings.

The transition to a family foster care system presents challenges, requiring highly specialised child welfare services to address the unique needs of families and children [6]. Notably, the pitfalls in child welfare reforms are, in part, attributed to rapid changes that rely on unprepared staff and evidence-practice gaps [7]. Child welfare practice models, conceptual maps rooted in values, can contribute to addressing these challenges. These frameworks help specify and operationalize caseworkers’ skills and practices through different stages of the child welfare continuum [8, 9]. As such, child welfare practice models have been found to enhance consistency in practice [10], facilitate the achievement of case goals and family engagement [11], and improve children’s outcomes when implemented with fidelity [12].

In Portugal, the Integrated Model of Family Foster Care (MIAF) has recently emerged as a pioneering child welfare practice model to respond to the demands of a paradigm shift to a family foster care system. MIAF is designed to encompass the complete continuum of family foster care, focusing on aspects from the recruitment, training, assessment, and selection of foster families to the placement of children in foster care and their subsequent transition to a permanent solution, such as family reunification or adoption. Aligned with national laws, MIAF incorporates fundamental principles and intervention guidelines for each phase of family foster care. With multiple teams in the country starting to implement this model, it aligns with principles emphasized in implementation science frameworks [e.g., 13]. These frameworks advocate for a stage-based approach, prioritizing an initial focus on implementation process evaluations (e.g., fidelity) and child and family outcomes rooted in a well-defined theory of change before progressing to more advanced stages, including effectiveness testing and full-scale implementation [8, 13]. This methodical and comprehensive approach allows for crucial adjustments to be made to child welfare practice models before scaling-up. The focus of this research is to investigate MIAF as a novel child welfare practice model aimed at promoting high-quality foster family care in Portugal.

From a process evaluation perspective, spanning multiple levels, various factors can influence the successful implementation of a new model, such as MIAF [14]. These factors may relate to the provider (e.g., knowledge and relational skills), the innovation itself (e.g., flexibility), the client (e.g., outcomes), the organization (e.g., leadership), and the process (e.g., fidelity feedback). Identified factors can potentially act as barriers, limiting adherence to the new child welfare practice model [15, 16]. In the Portuguese context, the urgency to identify such factors is compounded by the complex, often crisis-oriented dynamics that child welfare workers must navigate. Moreover, the prevailing lack of a family foster care culture in the country [17], coupled with stakeholders’ negative perceptions of family foster care [18], underscores the significance of mapping these multi-level factors for informed decision-making in the ongoing implementation of MIAF.

Despite the significant implications for child safety, stability, and overall well-being, many studies on child welfare practice models have neglected comprehensive outcome evaluations, leaving unanswered questions regarding their effectiveness in empowering families. Recent evidence suggests that foster parents may experience distress [19] and decreased responsiveness [20] during the crucial first year of placement, a period intricately linked to child outcomes such as behavior problems [21], attachment disorders [22], and placement instability [23]. Research also underscores the importance of examining the dynamic interplay between child and family factors [24], highlighting the significant impact of both child-related factors (e.g., behavior problems) and family-related variables (e.g., stress, mental health) at the time of placement on caregiving quality. This, in turn, may adversely affect child outcomes [19, 20, 21]. Yet, the extent to which child welfare practice models serve as buffers, mitigating the impact of these early risk factors and safeguarding children, remains inadequately explored.

### Objectives of the research study

This research, guided by the Getting To Outcomes framework [8], aims to investigate the initial implementation stage of the MIAF, a child welfare practice model recently developed to address the current national priority in child welfare policies in Portugal. The goal of the MIAF is to promote high-quality family foster care practice standards and support families and children in achieving safety, stability, and well-being outcomes. Therefore, this study seeks to conduct a mixed-method process and outcomes evaluation. In terms of process evaluation, our objectives are to (1) determine whether the MIAF is being implemented as planned (i.e., with fidelity) and assess its feasibility, appropriateness, and acceptability, and (2) identify enablers and barriers to MIAF implementation. For outcome evaluation, our objectives are to (3) describe the developmental trajectories of foster care children enrolled in the MIAF, assess their safety and stability, and (4) examine the trajectories of foster parents’ well-being and the quality of relational care. Additionally, we aim to (5) evaluate whether the MIAF mitigates the potential negative impact of early risk factors at the child (e.g., behavior problems) and family (e.g., stress, psychological symptoms) levels, measured at the time of placement, on subsequent outcomes assessed up to 12 months post-placement.

## Methods

### The Integrated Model of Family Foster Care (MIAF)

The Integrated Model of Family Foster Care (MIAF) is a comprehensive framework designed to address the transition to a family foster care system in Portugal, ensuring high-quality services to meet children’s needs and support both foster and birth families. Developed by ProChild CoLAB and Santa Casa da Misericórdia de Lisboa, MIAF relies on an iterative process between researchers’ and child welfare practitioners’ expertise, fostering a collaborative approach. MIAF aims to enhance the professional and institutional practices of family foster care by promoting a common language and shared thinking, evidence-based practices, and the development of technical and relational competencies. These efforts are expected to positively impact children’s well-being and safety, as well as the (co)parenting skills of foster and birth families, and the relationships between the child, foster family, birth family, and caseworkers. MIAF incorporates a comprehensive training program for caseworkers, comprising initial training sessions, ongoing supervision, and continuous training throughout the implementation of the model. This approach ensures that caseworkers are equipped with the necessary knowledge and skills to effectively implement MIAF and provide high-quality support to foster families and children in care.

MIAF adopts a child-centered and trauma-sensitive approach [25], aiming to provide a secure base for children in foster care and promote adaptive developmental trajectories and relational permanency [26]. This focus on stable relationships contributes to a strong sense of belonging, identity, and life continuity for foster children. MIAF encompasses key processes across the entire spectrum of family foster care, each tailored to achieve specific objectives: (a) recruitment, training, assessment, and selection of foster families, designed to cultivate high-quality foster parenting by identifying, training, and assessing suitable candidates to become foster families; (b) matching children with foster families—this process guides decision-making to ensure the best match between a child in need and a suitable foster family, taking into account the child’s unique needs and circumstances; and (c) foster care placement and transition to a permanent placement—this process focuses on facilitating high-quality coparenting care, e.g. by engaging both foster and birth or adoptive families in shared caregiving responsibilities. The goal is to ensure a smooth transition for the child from foster care to a permanent placement, promoting stability and continuity of care.

### Overview of the research design

The research project employs a multi-method approach, incorporating both qualitative and quantitative data collection methods, along with a multi-informant approach. Process evaluation data for the MIAF key processes will be collected at two points: pre-placement (M1) and post-placement (M2). Outcome evaluation data will be collected longitudinally over the first 12 months of the child’s placement in foster care. The study will recruit 25 caseworkers engaged in implementing the MIAF from four child welfare agencies situated in the north and south of Portugal. Additionally, 100 children aged 0–9 years entering foster care and their respective foster families receiving the MIAF will be included in the study. It is expected that this sample will cover nearly the entire population served by the four foster care agencies participating in the study. The recruitment period for participants will extend from March 2024 until December 2025.

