#### Process evaluation—Quantitative methods

Informed by previously validated measures of implementation outcomes [28], a set of questionnaires were developed specifically for this project to assess fidelity, feasibility, and acceptance of MIAF implementation. Both caseworkers and foster families will complete these questionnaires online at different time points, including pre-placement (M1) and post-placement (M2). Regarding M1, data will be collected (a) after informative sessions for awareness raising and foster family recruitment, (b) after pre-service training, and (c) after the assessment and selection of foster families. For M2, questionnaires will be completed (d) one month following the child’s placement to assess child-foster family matching and the transition to family foster care processes, (e) at six months of placement to evaluate support during family foster care, and (d) one month following the child’s transition to a permanent solution. The number of items per questionnaire, rated on either a 3-point or 5-point scale, varies depending on the MIAF key process and informant (i.e., caseworker or foster family).

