
#### Child safety and permanency

Child safety and stability will be assessed by caseworkers using questionnaires specifically developed for this research project, drawing on previous work [38]. For *child safety*, which pertains to safeguarding children from harm, abuse, neglect, and various risks that may jeopardize their physical, emotional, or psychological well-being, caseworkers will evaluate both the physical and emotional environments within foster care over the preceding three months. The questionnaire comprises seven items rated on a 5-point scale, ranging from 1 (never) to 5 (always). Regarding *child stability*, which concerns the consistency and permanency experienced by a child in foster care, caseworkers will assess relational permanency. This involves evaluating emotional security (6 items), which pertains to the child’s opportunities to develop a sense of comfort and emotional support within the foster family, and claiming (4 items), which relates to the child’s opportunities to develop a sense of ownership and belonging within the family. Responses will be rated on a 5-point scale from 1 (totally disagree) to 5 (totally agree). Additionally, caseworkers will record incidents of placement breakdown (e.g., termination of foster care and reasons) and details about parental contacts (e.g., frequency of visits).

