#### Sociodemographic information

Sociodemographic data of caseworkers (e.g., years of experience), children (e.g., age and sex; but also, e.g. exposure to early adversities, such as neglect and abuse) and their foster families (e.g., duration of fostering experience, number of children they are fostering) will be collected at the beginning of their participation in the study.

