### Data analysis plan

The project will gather a comprehensive dataset, requiring an analytical strategy that encompasses both qualitative and quantitative data analysis techniques. For qualitative data analysis, we will employ thematic analysis using a deductive-inductive approach, grounded in theoretical and empirical knowledge on the topic. We will follow recommended guidelines for coding, such as the Braun and Clarke step-based approach [47], and reporting, such as the Consolidated Criteria for Reporting Qualitative Research (COREQ) Checklist. Qualitative analysis will be facilitated using software such as NVivo and MAXQDA.

Regarding quantitative data, diverse analytical approaches will be employed. Descriptive analysis will examine demographic characteristics and study variables, presenting mean ± standard deviation (SD) for continuous variables and frequencies (n) and percentages for categorical variables. Correlational analysis will use Spearman and Pearson correlations, while the chi-square test will assess nominal variables. Growth Curve Modeling will examine the developmental trajectories of children in family foster care by analyzing their initial status and considering time-varying predictors (e.g., early adverse experiences, quality of care). Additionally, trajectories of family well-being will be examined. Moderation analyses will examine the influence of the MIAF (e.g., fidelity) on the relationship between predictors and outcome variables. Specifically, these analyses will explore the moderating effect of the MIAF model on the relationship between early child and family risk factors and subsequent outcomes. Statistical significance will be set at *p* < 0.05. Quantitative analysis will utilize software such as SPSS version 29.0 (SPSS Inc., Chicago, IL, USA) and R Statistics.

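### Children are nested under 25 caseworkers in four agencies, but no named analysis carries a level above the child; tests of fidelity and of caseworker-rated outcomes can therefore be anti-conservative

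*Protocol article*

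**What the plan says.** **Structure.** Under Overview of the research design, the article states "The study will recruit 25 caseworkers engaged in implementing the MIAF from four child welfare agencies situated in the north and south of Portugal", and then "100 children aged 0–9 years entering foster care and their respective foster families receiving the MIAF will be included in the study". It adds: "It is expected that this sample will cover nearly the entire population served by the four foster care agencies participating in the study".

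**Who reports what.** Under Process evaluation—Quantitative methods, caseworkers and foster families both complete the fidelity questionnaires. The post-placement rounds are timed from each child's placement or transition. Under Child safety and permanency: "Child safety and stability will be assessed by caseworkers using questionnaires specifically developed for this research project". So the same professional may supply both the fidelity report and the outcome rating for several children.

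**Families.** Under Sociodemographic information, the background variables for foster families include "number of children they are fostering".

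**Analysis.** The Data analysis plan names Pearson and Spearman correlations, chi-square tests for nominal variables and growth curve models. It then says: "Moderation analyses will examine the influence of the MIAF (e.g., fidelity) on the relationship between predictors and outcome variables". These moderation analyses serve objective 5, whether MIAF buffers early child and family risk. Significance is set at 0.05. No caseworker, agency or family term is mentioned, nor any cluster-robust standard error. The Limitations and challenges section does not mention clustering.

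**The concern.** Pearson, Spearman and chi-square tests in their standard form take each record as an independent unit. Children served by the same caseworker share that person's training, practice and rating habits, so their fidelity scores and caseworker-rated outcomes may resemble one another. If both variables cluster, the ordinary standard error is too small and the stated 5% level is exceeded.

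The most exposed analysis is moderation by fidelity. The study has no comparison group, and fidelity is the only example the plan gives of how MIAF enters the moderation model. If the effect of early risk differs between caseworkers by chance, a single-level interaction test can report that as an effect of fidelity. The article intends to use its results to refine MIAF, to inform policy, and to feed four improvement sessions held between data collection points. A spurious fidelity effect would therefore have practical consequences.

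**Working it through.** The article gives no ICC, effect size or power calculation, so there is no stated figure to reproduce. The check asks how far a nominal 5% two-sided test departs from 5% when caseworker clustering is ignored. Two-sided testing is assumed, because the article does not say.

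**Inputs from the article:** 100 children, 25 caseworkers, 4 agencies, alpha 0.05. Mean cluster size m = 100/25 = 4 per caseworker and 100/4 = 25 per agency, if spread evenly.

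**Assumed inputs:** outcome ICC ρy = 0.05, 0.10, 0.20; predictor ICC ρx = 1 (fidelity constant within caseworker), 0.5 (half its variance within caseworker) and 0 (no caseworker clustering).

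**Formulas:**
- design effect DE = 1 + (m − 1)·ρx·ρy
- true standard error = √DE × naive standard error
- true alpha = 2·[1 − Φ(1.96/√DE)]

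**Association test at caseworker level, m = 4.** The simulated column is a Pearson test with 20,000 runs of 25 clusters of 4.

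| ρy | ρx | DE | √DE | alpha, formula | alpha, simulated |
|---|---|---|---|---|---|
| 0.05 | 1 | 1 + 3×0.05 = 1.15 | 1.07 | 6.8% | 6.8% |
| 0.10 | 1 | 1 + 3×0.10 = 1.30 | 1.14 | 8.6% | 8.8% |
| 0.20 | 1 | 1 + 3×0.20 = 1.60 | 1.26 | 12.1% | 12.4% |
| 0.05 | 0.5 | 1 + 3×0.025 = 1.075 | 1.04 | 5.9% | 5.9% |
| 0.10 | 0.5 | 1 + 3×0.05 = 1.15 | 1.07 | 6.8% | 6.6% |
| 0.20 | 0.5 | 1 + 3×0.10 = 1.30 | 1.14 | 8.6% | 8.8% |
| any | 0 | 1.00 | 1.00 | 5.0% | about 5% |

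With fidelity constant within caseworker, the effective number of children is 100/DE = 87, 77 and 62.5.

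**Unequal caseloads.** With an assumed coefficient of variation of 0.6 and ρx = 1, DE = 1 + (1.36×4 − 1)·ρy = 1.22, 1.44 and 1.89. Uneven spread makes the problem somewhat larger.

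**Fidelity-by-risk interaction.** This was simulated with ordinary least squares, 25 caseworkers of 4 children and no true interaction. The effect of risk was allowed to vary between caseworkers, with assumed slope variance of 5%, 10% and 20% of total variance.
- Fidelity constant within caseworker: false positives about 8%, 10% and 15%.
- Half of fidelity's variance within caseworker: about 7%, 8% and 12%.
- Caseworkers differing only in their mean level (ICC 0.20, no slope variation): about 5%.

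In this setting the interaction test is threatened by variation in slopes, not in means. A random intercept alone would not protect it.

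**Shared foster families.** If 20% of children were in pairs with family ICC 0.5 (both assumed), the average DE is 1 + 0.20×0.5 = 1.10.

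**The case against.** **The plan does not say that children are treated as independent.** This stands for the growth and moderation models. A growth curve model can take higher levels, an article condenses its full protocol, and a fuller analysis plan may specify them. For these models the point is that no level above the child is stated, not that a wrong one is chosen. It stands less well for the correlations and chi-square tests, which are named methods that assume independent units. The article does not, however, assign those tests to the fidelity question.

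**Fidelity is not shown to be a caseworker trait.** This stands. Foster families report it too, and post-placement rounds follow each child, so it can vary within caseworker. A reader might infer that fidelity carries the information of only 25, or even 4, units. That is the extreme case and the article does not support it.

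**The agency-level figures are worst case.** With m = 25 and agency ICC 0.02 or 0.05, DE is 1.48 or 2.20 and true alpha 10.7% or 18.6%. That requires fidelity to be identical for all 25 children in an agency, which the placement-level and family reporting makes implausible.

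**Shared families are only implied.** This stands. Recording how many children a family fosters does not show that two study children live together, and the calculated effect is small.

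**Caseloads are an average.** This also stands. No caseload or one-rater rule is given, and some caseworkers may mainly handle recruitment or selection of families.

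**The sample covers nearly the whole agency population.** This does not remove the problem if p-values are meant to speak beyond these particular caseworkers.

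**Conclusion.** The point holds in a conditional form. The nesting is documented, caseworkers supply both a key predictor and two outcomes, and no named analysis states a level above the child. Applied as written, the tests are anti-conservative where predictor and outcome both cluster by caseworker. That chiefly concerns fidelity, and safety and stability as rated by caseworkers.

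The size is modest to moderate. Over outcome ICCs of 0.05 to 0.20, true error runs from about 6% to 9% with half of fidelity's variance within caseworker, and from about 7% to 12% with fidelity constant within caseworker. All ICCs and slope variances are assumptions, and clusters of 4 assume an even spread.

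A reader might conclude that every standard error in the study is too small. The article does not support that: for predictors varying only between children, the naive test keeps about 5%.

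**What to change.** In the Data analysis plan:
- Add a caseworker random intercept and agency as a four-level fixed effect to the growth and moderation models. Four agencies are too few for a reliable agency random effect or agency-clustered standard errors.
- Split fidelity into a caseworker mean and a within-caseworker deviation, and report both coefficients.
- For the fidelity-by-risk test, add a caseworker random slope for risk where it can be estimated, with small-sample inference such as Kenward-Roger.
- For child-level associations reported with p-values, replace plain correlation and chi-square tests by the same mixed model, or by a cluster-robust method with a small-sample correction and caseworker as the cluster. Uncorrected GEE or bootstrap with 25 clusters can itself be anti-conservative.
- If two study children share a foster family, use one record per family for family-level outcomes. A family random intercept beside a child intercept would be hard to estimate if most families have one study child.

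The cost is analysis wording, provided each child's record carries caseworker, agency and family identifiers. The data sources imply these, but the article does not state it. Intervals will be somewhat wider. With about 100 children the full random-effects structure may not converge, so the order in which terms would be dropped should be written down beforehand.
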